### Primary endpoint

2.13

The primary endpoint is the relative risk of an acute hospital readmission in the 30 days following discharge for intervention group patients compared with control group patients (Hypothesis 1). The relative risk of readmission rather than readmission rate ratio was chosen as the primary endpoint because risk (probability of readmission within specified period) is easier to measure as it just requires counting the first time a patient is readmitted. By only counting the first readmission we avoid patients with large numbers of readmissions having a disproportion impact on the endpoint measure. This also simplifies statistical analysis. We have included the hazard ratio of readmission as a secondary endpoint (see below).

We will measure ethnic-specific differences in the primary endpoint measures and differences according to a 30-day^2^ readmission risk for Māori and non-Māori patients (combined).

To determine the superiority limit for the purposes of sample size calculations it was considered that the Harti programme should deliver at least a 7% absolute decrease in overall readmission risk as this would be both clinically meaningful for tamariki and whānau and financially meaningful for the hospital. Furthermore, we have designed the study so that it has power to detect a 12% absolute decrease in the 30-day risk of readmission for the Māori population. It is not powered to detect differences in risk of readmission between Māori and non-Māori tamariki.

### Additional pre-specified analyses of an exploratory nature, based on the primary endpoint

2.14

These will include the following:
➢The **hazard ratio** for (first) readmission in the intervention group compared with the control group. This compares time to the first readmission rather than just the fact of a readmission. As such, it can make use of varying lengths of follow-up time and may be more sensitive to the impact of the intervention. However, the use of the hazard ratio relies on the proportional hazards assumption, which is that the relative hazard of readmission remains constant over time.➢The **relative risk** of any readmission within 30 days of discharge, and from one to six months from the index admission event. This will examine whether the observed effect of the intervention on readmission rates occurs with a short or medium period. These analyses are exploratory as the trial has not been powered to detect difference within these time frames (although it may have adequate power to do so).➢A simple **Kaplan–Meir analysis** to compare the “survival” functions of intervention and control groups where survival in this case is taken to mean time following discharge without hospital readmission. For exploratory analysis of relative 6- and 12-month readmission risks this will also be used.➢Relative 30-day readmission risk in children aged less than 1 year at the time of their index admission (Hypothesis 1a). This outcome was added as a pre-specified analysis on the grounds that the interrupted time series analysis of the pilot suggested that the impact of the intervention is strongest (and possibly restricted to) this age group.

### Secondary endpoints

2.15

There are seven quantitative secondary endpoints. Pre-testing will be undertaken to ensure that data can be accessed (e.g., GP enrolment and WCTO records) for all study endpoints.

### Whānau satisfaction with care

2.16

Hypothesis 2 examines the difference in satisfaction with hospital experience between the intervention and control groups. This will be measured using the first seven questions from the Mārama real-time survey. Two questions have been added for the purposes of this research: one on the responsiveness to whānau needs, the other on whether a holistic approach was employed (Figure 3). An tenth open-ended Mārama question will also be asked and analysed. The responses will be scored on a 5-point Likert Scale ranging from Strongly Disagree to Strongly Agree (1 point for the former, 5 for the latter), so the total possible score range for someone answering all questions is from 9 to 45 which will be scaled to a range of 0–100 to accommodate cases where one or more questions is not responded to. The responses will be provided by the child’s primary care-giver.

**Figure 3 F3:**
[figure not shown]
Patient satisfaction with hospital care (mārama survey).

### Preventative health care

2.17

These hypotheses (3a & 3b) examine the difference in preventive services access and utilisation between the intervention and control groups. As previously mentioned, important universal preventative care is provided in the 0–4 year age group and for this reason these variables were chosen as secondary outcomes; general practice enrolment, oral health care, immunisations, and WCTO visits.

This endpoint has two parts: **documentation** and **achievement**. For documentation, external sources will be used to determine whether at admission the child was (i) enrolled with a General Practitioner (GP); (ii) enrolled with the oral health services; (iii) up to date with all oral health checks (seen in the last 12 months); (iv) up to date with all immunizations; (v) up to date with WCTO visits. The indicator that will be compared between the intervention and UC groups is the number of children with ‘non-compliance’^3^ in any of the five domains (GP enrolment, oral health enrolment, up-to-date oral health checks, up-to-date immunisation, and up to date WCTO visits). In whom compliance is achieved (fully documented in the intervention assessment or patient record during the child's admission), divided by the total number of children with non-compliance in any of these five domains.

For the **achievement** component of this endpoint (hypothesis 3b), which is contingent on detecting a significant difference in the **compliance** component, intervention and UC groups will be compared on the proportion of children who at admission were non-compliant on any of the five domains, and who became fully compliant within 30 days of discharge from the hospital. Fully compliant is defined as all of the following; enrolment with a GP, enrolment in oral health services, a completed or booked oral health check, complete on the pathway for immunisation (for age) and complete WCTO participation.

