### Design

2.2

The study uses a Kaupapa Māori methodology with qualitative and quantitative methods. Qualitative methods include in-depth interviews with whānau and are published elsewhere (24). Quantitative methodology was a randomised controlled observer-blinded parallel groups single centre superiority trial. It is designed to measure the impact of the Harti tool, compared with usual hospital care, on child and whānau wellbeing outcomes, as specified in the primary and secondary endpoints. Tamariki and their whānau will be randomised to the intervention and control groups at a ratio of 1:1. The intervention group will receive usual care plus the Harti tool, and the control group will receive usual hospital care only, as per the trial schematic shown in Figure 1.

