### Sample size calculation

2.8

We aim to recruit a total of 1,000 participants, of whom we expect approximately 40% will be Māori (based on current figures and expected acceptability of the research protocol). This sample has been calculated to ensure that there is sufficient statistical power to detect a 7% absolute reduction in the 30-day readmission risk in the intervention group for all children and a 12% absolute reduction in the 30-day acute readmission risk for Māori. Sample size calculations are based on a two-tailed 0.05 level of significance with 80% power. We assume that the acceptability of participation will be similar for Māori and non-Māori.

We will measure differences between the intervention and control groups in the primary endpoint (readmission risk) controlling for age, sex, residing in Hamilton, socioeconomic deprivation (NZiDep), and RA responsible for conducting the intervention. Analyses of the primary endpoint will be stratified by ethnicity.

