### Data handling and monitoring

2.23

Analysis will be performed on an intention to treat basis. That is, endpoints will be compared for the two groups as defined from the point of randomisation to intervention or control group. For the primary endpoint, participants who are readmitted multiple times from each group will be included in the analysis only for the first (valid) occasion on which they are readmitted in the 12 months following the index admission.

Bivariate analyses comparing groups will test for statistical significance using the Chi Square test for differences in proportions. For the length of stay secondary endpoint where a difference in medians is to be tested, the Mann–Whitney *U* test will be used.

Although the randomised design is expected to yield balanced intervention and control groups in a study of this size, logistic regression analysis will be used for the primary and secondary endpoints to control for important confounding variables and to facilitate the assessment of interaction variables that increase or decrease the efficacy of the Harti tool. Statistical significance will be tested at the alpha level of 0.05. We will control for the false discovery rate in the secondary endpoints using the Benjamini–Hochberg method (39).

The study is not powered to detect ethnic differences in the impact of the intervention (effect modification). However, we will nevertheless conduct exploratory tests for effect modification with ethnicity (Māori/non-Māori), gender (male/female excluding other), and deprivation (as a dichotomised variable) using the Breslow Day test for homogeneity of odds ratio, and standard maximum likelihood methods (likelihood ratio tests) based on binomial regression models. We will assume an additive interaction for these analyses and report the relative excess risk due to interaction (RERI) where this is significant effect.

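### Hypothesis 3b counts only children with every gap closed, yet the number of gaps at admission, already obtained, is not named for use in its analysis; adjusting for it is a modest, nearly free gain

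*Protocol article*

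**What the plan says.** Under Preventative health care (2.17), admission status is established on five domains: GP enrolment, oral health enrolment, oral health checks, immunisation and WCTO visits. The source is stated: "external sources will be used to determine whether at admission the child was" enrolled or up to date on each. Children with a gap in at least one domain form the denominator.

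For the achievement part (3b), the arms are contrasted by the share of participants "who at admission were non-compliant on any of the five domains, and who became fully compliant within 30 days of discharge". Full compliance is then defined as meeting all the listed domains, so closing three gaps out of four counts as failure. 3b is tested only if the first component shows a significant difference.

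Data handling and monitoring (2.23) gives a chi-square test for proportions and adds that "logistic regression analysis will be used for the primary and secondary endpoints to control for important confounding variables". Those variables are not listed there. The one named list is in Sample size calculation (2.8), where the primary endpoint is compared "controlling for age, sex, residing in Hamilton, socioeconomic deprivation (NZiDep), and RA responsible for conducting the intervention". It contains no service status at admission, but it is written for readmission and not for 3b.

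**The concern.** Under an all-or-none rule, the number of gaps a child starts with largely sets how hard success is. If each gap closes independently with probability 0.5, a child with one gap succeeds 50% of the time and a child with five gaps 0.5^5 = 3% of the time. A baseline variable of that strength is worth using in the comparison, and here it is already in hand for every child in the 3b denominator.

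The plan justifies regression as control of confounding. Gap number is balanced by randomisation on average, so someone choosing covariates strictly as confounders could pass over it, although its value here is prognostic. Randomisation is also simple and unstratified, so some chance imbalance in gap number can arise in any one trial, and the raw chi-square takes no account of it.

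At stake is the precision of one gated secondary endpoint, for which the trial was not sized.

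**Working it through.** **1. The plan's own figure.** "We aim to recruit a total of 1,000 participants, of whom we expect approximately 40% will be Māori", allocated 1:1, which gives 500 per arm. "Sample size calculations are based on a two-tailed 0.05 level of significance with 80% power", for a 7-point absolute reduction in 30-day readmission. The control risk is not stated. With 500 per arm, power for 7 points is 0.85, 0.80, 0.77 and 0.71 at control risks of 20%, 22.9%, 25% and 30%. The figure is plausible but cannot be confirmed, and it does not bear on 3b, for which no power is claimed.

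**2. Is power scarce for 3b?** Table 2 seeks at least a 25% increase without saying whether this is relative or absolute. I use n per arm = [1.96·√(2p̄(1−p̄)) + 0.84·√(p0(1−p0) + p1(1−p1))]² / (p1−p0)², with p̄ the mean of p0 and p1, for 80% power at two-sided 0.05.

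| Control | Relative 25% | n per arm | Absolute 25 points, n per arm |
|---|---|---|---|
| 20% | 25% | 1,094 | 54 |
| 30% | 37.5% | 623 | 61 |
| 40% | 50% | 388 | 62 |
| 50% | 62.5% | 247 | 58 |

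At most about 500 per arm exist and only children with gaps count. On the relative reading power is scarce at lower control rates; on the absolute reading it is ample.

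**3. One scenario by hand.** Assumptions, none in the documents: 300 children with gaps per arm; 1, 2, 3, 4, 5 gaps in 40, 30, 15, 10, 5% of them; each gap closed independently with probability q = 0.5 (usual care) or 0.6 (intervention).

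- Usual care: 0.40(0.5) + 0.30(0.25) + 0.15(0.125) + 0.10(0.0625) + 0.05(0.03125) = 0.302.
- Intervention: 0.40(0.6) + 0.30(0.36) + 0.15(0.216) + 0.10(0.1296) + 0.05(0.0778) = 0.397.
- Outcome variance explained by gap number, usual care: mean of q^(2k) is 0.1215, so (0.1215 − 0.3016²) / (0.3016 × 0.6984) = 0.0306 / 0.2106 = 0.145. In the intervention arm it is 0.0341 / 0.2394 = 0.142. Average 0.144.
- Unadjusted: difference 0.0957, null SE 0.0389, alternative SE 0.0387. (0.0957 − 1.96 × 0.0389) / 0.0387 = 0.50, power 0.69.
- Adjusted, approximately: SE shrinks by √(1 − 0.144) = 0.925. 0.0957 / (0.0387 × 0.925) − 1.96 = 0.71, power 0.76.

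Simulation of the same scenario (1,500 trials, error about 1 point) gave 0.685 for the unadjusted test and 0.767 for logistic regression with gap number.

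**4. Dropping independence.** A second simulation, with 10,000 trials per scenario and 250 per arm, compared the chi-square with a Cochran-Mantel-Haenszel test stratified by gap number. It added a child random effect on the logit scale to link closures within a child. Rows below use per-gap closure 0.5 and a per-gap odds ratio of 1.6; entries are chi-square power → stratified power.

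| Gap distribution | SD 0 | SD 1 | SD 2 |
|---|---|---|---|
| Mostly one gap | 0.75 → 0.79 | 0.60 → 0.61 | 0.37 → 0.37 |
| Mixed | 0.75 → 0.81 | 0.59 → 0.63 | 0.37 → 0.37 |
| Even spread 1 to 5 | 0.72 → 0.80 | 0.58 → 0.63 | 0.36 → 0.38 |

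Over all gap distributions and closure rates of 0.3, 0.5 and 0.6, the gain was +3 to +8 points at SD 0 (worth about 8 to 22% more children), +1 to +5 at SD 1 (3 to 12%), and −1 to +1.5 at SD 2. Type I error was held, at 0.043 to 0.051.

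**5. 3a.** If the tool documents about 90% of cases against 20 to 60% in usual care, 7 to 32 children per arm suffice, and there is little power to recover.

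**The case against.** The strongest reply is that covariate lists belong in the SAP. The protocol already commits to regression for secondary endpoints and does not exclude the gap count; it only leaves it unnamed. The sentence on confounding opens with expected balance, so it may loosely mean any baseline variable that predicts outcome. This stands against any claim that the plan is wrong or that power is being discarded. It does not remove the value of naming the variable, since the endpoint rule and the data source are both fixed in the protocol and together point to it.

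Second, independence is a favourable assumption. Oral enrolment and oral checks are two of the five domains, and one research assistant works through all needs with the family. With one linked pair of domains, the scenario in step 3 gave 0.71 → 0.755; adding a child effect gave 0.555 → 0.57 (SD 1) and 0.33 → 0.325 (SD 2). This stands, and it is why the range runs down to nil.

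Third, the comparator above is a bare chi-square. Against a regression that already holds covariates correlated with gap number, the gain would be smaller. This also stands.

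A reader might infer that 3a loses power in the same way. The documents do not support that: the 3a sentence is broken, so all-or-none is only one reading of it, and the tool itself does the documenting, so the contrast is probably large.

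**Conclusion.** The point holds for 3b as an optional gain in efficiency. Success depends by construction on the number of gaps at admission, the trial obtains that number for both arms, and no stated analysis names it. With 250 to 300 children with gaps per arm, the expected benefit is about 3 to 8 power points if gaps close independently, about 1 to 5 with moderate correlation within a child, and about nil with strong correlation. The worst simulated result was a loss of about one point, so there is no material downside. The number of children with gaps, the gap distribution, the closure rates and the correlation are all assumed. If the 25% in Table 2 is absolute, power for 3b is ample and the gain matters little.

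A reader might infer that the chi-square result would be biased. It would not: gap number is a pre-randomisation variable and omitting it leaves the randomised comparison valid. Nor does the point call for a graded or per-gap endpoint. That would gain more power but would answer a different question.

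**What to change.** Keep the 3b endpoint and its denominator. State in the SAP that the main 3b analysis is the logistic regression already planned, with the number of non-compliant domains at admission (1 to 5) as a prespecified covariate or stratum. Report a risk difference or ratio standardised over the observed gap distribution, because the adjusted odds ratio is conditional on gap number and is not the contrast in proportions that 3b describes. Keep the chi-square as a supporting result. The same adjustment may be applied to 3a for consistency, with little or no gain expected.

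The cost is a sentence or two in the SAP, settled before allocation is unblinded. The variable comes from the admission status already drawn from external sources, and the matching to service databases is already done blind to allocation.

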As a response to these issues of unmet health need and inequitable and unacceptable hospital readmission rates for tamariki Māori in the Waikato, Te Puna Oranga (the Māori Health Unit) at Te Whatu Ora Waikato led a co-design process with nurses, Kaitiaki (cultural support workers) and doctors who had worked or were working in child health at Waikato Hospital (11). The co-design process resulted in the development of a tool to identity health and wellbeing needs, and to support opportunities to address need and enable the provision of holistic and preventative care particularly for hospitalised tamariki Māori and their whānau. The Harti Tool was added in a paper folder to patient notes and used in the paediatric medical wards at Waikato Hospital from 2014 to 2017. The paediatric medical charge nurse reported that the majority of patients and their whānau were provided access to a wellbeing needs assessment using the tool during this time.

The team presented the Harti approach to colleagues around the country at peer meetings, conferences and seminars. The tool was shared freely with all people and groups who requested it. As a result, the tool was implemented in other areas around the country. After the Harti tool had been in place for 3 years, the team decided to apply for a Health Research Council of New Zealand grant to measure the impact of the tool. Another driver was the need to update the screening questions and follow up protocols in the tool and to further develop thinking around the model of care for the tool.

This paper describes the protocol for the quantitative evaluation of the effectiveness of the Harti Tool using a randomized controlled trial (RCT). Objectives of the RCT (the “Harti RCT”) are:
➢To provide a quantitative measure of the effectiveness of the Harti tool➢To determine the level of unmet need identified by the Harti tool, and➢To assess the impact of the Harti tool on meeting those needs and achieving improved outcomes for tamariki.

The Harti RCT aims to answer the following research questions compared with usual care;
➢Does the use of the Harti tool increase documentation of assessment of health and non-health needs?➢Does use of the Harti tool result in a lower readmission risk for hospitalised children?➢Does the Harti tool improve satisfaction with hospital experience?➢Does the Harti tool increase access to and utilisation of wellbeing services?

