### Intervention procedure

2.10

The intervention will consist of a 24-section tool with screening questions and follow-up protocols for each question in accordance with the process shown in Figure 2. Intervention group patients and their whānau are invited to go over the Harti tool with the RA and provided with an information and activity booklet (whānau booklet). After engagement, RAs will go through the Harti tool on a tablet. RAs will read out questions in order and fill in answers for participants, in some cases participants may view questions and select responses themselves, if they prefer. The RA will follow established protocols to follow up on any identified areas of need. For example, if a child is not enrolled with a particular service, the RA will offer to assist with enrolment; if the patient or another child present or at home is identified to have a sore throat, then Rheumatic Fever prevention protocols will be followed. RA's will have equipment (cell phones and an iPad) to enable referrals and enrolments to take place at the bedside or in the interview room. The Harti RA will be trained in delivering high quality smoking cessation interventions for whānau and safe sleep devices including Pēpi Pods will be made available. If the whānau are not sure of the child's enrolment status (anecdotally a common occurrence), the Harti RA will match the patient’s National Health Index (NHI) number with selected databases and double check for access or check enrolment with the service over the phone or directly, e.g., oral health services.

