### Measures of effectiveness

2.12

A summary of each research hypothesis is listed in Table 2 and the details of how these will be examined is below.

**Table 2 T2:** The primary (1, 1a) and secondary endpoint hypotheses summarised for the trial outcome data.

Hypothesis number	Hypothesis
1	Use of the intervention will result in a 7% lower readmission risk at 30-days for children aged 0–4 admitted to hospital for the intervention group compared to the usual care group.
1a	Use of the intervention will result in a 5% lower readmission risk at 30 days for children aged under 12 months admitted to hospital for the intervention group compared to the usual care group.
2	The intervention will result in a 5% higher satisfaction with hospital experience score for the intervention group compared to the usual care group.
3a	Compared to usual care, the intervention assessment will result in at least a 50% increase in the full documentation of non-enrolment with a GP, non-enrolment in oral health services, not up-to-date oral health checks, incomplete immunisation (for age) and incomplete WCTO participation.
3b	Compared to usual care, the intervention assessment will result in at least a 25% increase in full compliance with GP enrolment, oral health service enrolment, oral health checks, immunisation and WCTO participation.
4	Compared to the UC group, the intervention group will have at least a 25% higher complete smoking cessation referral rate for households with a documented resident who smokes.
5	The intervention group will have at least a 25% higher complete Whare Ora referral rate compared with the UC group
6	The intervention group will have a significantly lower median cumulative length of hospital stay in all acute admissions in the 12 months following discharge from the index admission event compared with the UC group
7	The readmission rate in the intervention group will be 25% less than the readmission rate in the UC group.

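### H3b holds the oral-check item to a stricter standard at admission (seen) than at 30 days (a booking suffices), so a child can become fully compliant without a check

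*Protocol article*

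**What the plan says.** Section 2.17 of the Protocol article establishes each child's status at admission on five domains. For oral checks the standard is being "up to date with all oral health checks (seen in the last 12 months"). A booking is not mentioned.

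H3b, the achievement part of this endpoint, compares the arms by the share meeting this condition: "at admission were non-compliant on any of the five domains, and who became fully compliant within 30 days of discharge from the hospital". The section continues: "Fully compliant is defined as all of the following". The oral-check entry in that list is "a completed or booked oral health check".

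Table 2 (section 2.12) words the same hypothesis as "at least a 25% increase in full compliance with GP enrolment, oral health service enrolment, oral health checks, immunisation and WCTO participation", with no reference to bookings. Section 2.17 says that hypotheses 3a and 3b "examine the difference in preventive services access and utilisation between the intervention and control groups", and the Introduction asks: "Does the Harti tool increase access to and utilisation of wellbeing services".

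Section 2.10 has the research assistant follow up each need identified in an intervention family, with equipment to "enable referrals and enrolments to take place at the bedside". Section 2.11 gives controls usual care and the satisfaction survey.

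**The concern.** H3b counts a change of status. Such an endpoint is interpretable only if the same standard applies at both ends. Here the later standard is looser, so some changes of status come from the change of rule and not from anything that happened to the child.

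Two things are at stake. First, children who already held an appointment at admission can be scored as converted with no new action, which adds noise to both arms. Second, H3b is presented as achievement and as evidence on utilisation. A booking may show access, but it does not show that a service was used. If bookings arise more often where a research assistant is following up needs, the intervention arm can do better on H3b with no more children having been checked.

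**Working it through.** The document gives no rate, sample size or power for H3b, so there is no stated figure to reproduce. The check is a comparison of the two standards, followed by an illustration on assumed inputs.

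**Step 1: the two standards applied to four children.** Each was not seen in the 12 months before admission, and each meets the other four items by day 30.

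| Child | As written | Seen or booked at both times | Completed check only |
|---|---|---|---|
| A: no booking at admission, check done by day 30 | converts | converts | converts |
| B: no booking at admission, booked but not seen by day 30 | converts | converts | does not convert |
| C: booked at admission, not seen by day 30 | converts | oral item already met at admission | does not convert |
| D: booked at admission, check done by day 30 | converts | oral item already met at admission | converts |

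As written, H3b does not separate A from B or C. A common definition that accepts bookings removes C but keeps B. Only the completed-check version removes both.

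**Step 2: effect of already-booked children.** Let a share q of the denominator be children of type C. They add q to the H3b proportion in each arm. Randomisation should balance q, so the difference is unchanged and the ratio moves towards 1. With assumed proportions of 30% and 20% and q = 5%, the ratio goes from 0.30/0.20 = 1.50 to 0.35/0.25 = 1.40. This part does not favour the intervention.

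**Step 3: effect of new bookings.** Let
- c = proportion fully compliant with a completed check, equal in both arms;
- s = share of the denominator whose only outstanding item at day 30 is the oral check;
- b = share of those who are booked but not seen, by arm.

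The H3b proportion as written is c + s × b, so the apparent difference is s × (b_intervention − b_control). With a completed-check rule it is zero.

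All inputs here are assumptions. With c = 20%, s = 20%, and b = 50% to 80% (intervention) against 10% (control):
- control: 0.20 + 0.20 × 0.10 = 22%;
- intervention: 0.20 + 0.20 × 0.50 = 30%, up to 0.20 + 0.20 × 0.80 = 36%;
- ratio: 0.30/0.22 = 1.36, up to 0.36/0.22 = 1.64.

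With an assumed 200 children per arm in the denominator, a two-sided test at 0.05 would be significant with probability 45% to 87%, ignoring household clustering and the false discovery rate step.

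Across c = 10% to 30%, s = 10% to 30% and the same booking rates:
- the difference runs from 0.10 × 0.40 = 4 points to 0.30 × 0.70 = 21 points;
- the ratio runs from 0.35/0.31 = 1.13 to 0.34/0.13 = 2.62.

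This shows that the rule could produce an H3b difference by itself. It does not show that it will.

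**The case against.** A good deal can be said for the plan.

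- **Bookings by the research assistant are not stated.** A reader might infer that a bedside booking by the assistant is what H3b scores as success. Section 2.10 names referrals and enrolments, and its oral-health example concerns checking enrolment with the service. Booking is a reasonable inference from follow-up of needs and direct contact with services, but no more than that. This stands, and it is why the direction of any bias is put as possible.
- **The rule is the same for both arms.** Bookings count for controls too, and already-booked children should be balanced. This stands for Step 2. It does not settle Step 3, because the follow-up that may generate bookings exists in one arm only. Blinded database matching (section 2.24) does not help, since the booking itself would be genuine.
- **Access is part of the aim.** A booking is a sensible access marker in a 30-day window, and connecting families to services is what the intervention is for. Other endpoints count referrals openly (sections 2.18 and 2.19). This justifies reporting bookings. It does not justify a different standard at admission, or merging bookings with completed checks under a utilisation claim.
- **All five items are required.** A booking decides the result only when the oral check is the last gap. This stands and limits the effect.
- **The admission rule may be qualified elsewhere.** The wording about being seen is in the documentation part of section 2.17, and the footnote attached to non-compliance is not in the text at hand. H3b reuses the same five domains at admission, so the mismatch stands on the visible text, subject to that footnote.

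A reader might also want to state what fraction of an H3b effect consists of unattended bookings. That fraction would simply be one minus an assumed attendance rate, and the document gives no booking or attendance rates.

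**Conclusion.** The mismatch is explicit in section 2.17. As defined, H3b can count a child as having become fully compliant when no oral check took place, including on an appointment that predates the trial contact. Already-booked children inflate both arms. New bookings may favour the intervention arm, on the inference that follow-up by the research assistant leads to more of them.

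The size cannot be determined from the document; the 4 to 21 points above rest wholly on assumed inputs. The document does not support a claim that H3b is known to be biased by a given amount. It does support the narrower statement that H3b, as worded, cannot carry a conclusion about utilisation of oral health checks. The definition is fixed in the article, so this is not detail left to an analysis plan. It affects one of five components of a secondary endpoint, which is tested only if the preceding documentation part is significant. The primary endpoint is untouched.

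**What to change.** Make two changes in section 2.17.

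1. Use one oral-check definition at both time points, so that already-booked children are not counted as converted. For example: the item is met, at admission and at 30 days, if the child was seen in the preceding 12 months or holds a booking. Check this against the footnote on non-compliance first.
2. Report H3b a second time with the oral item met only by a completed check. Rest any utilisation claim on this version, and treat bookings as an access or process measure. The first change alone is not enough, because a new unattended booking would still count as success. State which version enters the Benjamini–Hochberg procedure of section 2.23.

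The cost is mainly wording and data. Booking and attendance dates are needed from the oral health service match; section 2.24 plans matching for enrolment and service use but does not mention booking dates, so their availability should be confirmed in the pre-testing announced in section 2.15. A few children leave the denominator, few checks may be completed within 30 days, and the apparent effect may be smaller.
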